**Figure 2. f2:**
[figure not shown]
Data sources of the planned study.

Extracted data from the selected hospital records and CRFs were to those from the Perined records of the same mothers and neonates in order to compare these two types of records. Data managers linked the records by matching several demographic variables (e.g. date of birth of the mother and postal code). Variables will be included in the current study if they are available in both Perined and either the extracted hospital record data or the CRFs.
Table 1 and
Table 2 show which variables will be compared. The categories of the variables will be created with data driven approaches. We expect that the data for these variables as derived from the respective source can be coded into the categories as shown in
Table 1 and
Table 2, or are already available in this way. The syntax comprising the respective coding steps will be published, after publication of the final results as planned in the current study. In case a good comparison between certain variables is not possible, they will be removed and not include in the comparative analyses.

**Table 1. T1:** Example|Descriptive statistics of the variables to be studied based on Perined and the hospital records/CRFs.

Variable ^1^					
Maternal variables (n=)	Perined data source ^2^	Perined n (%)	Missing n	Hospital records or CRFs* n (%)	Missing n
Maternal age *(mean (SD))*					
Maternal ethnicity					
Dutch					
Other					
Parity					
0					
1					
2					
3					
4					
>4					
Responsible profession at start of labour					
Midwife-led care					
Obstetric-led care					
Referral of care from midwife-led care to obstetric-led care during labour					
Yes					
No					
Responsible profession at birth					
Midwife-led care					
Obstetric-led care					
Start of labour					
Spontaneous					
Induction of labour					
Planned caesarean section					
Type of birth					
Spontaneous					
Assisted vaginal birth					
Planned caesarean section					
Unplanned caesarean section					
Epidural/spinal analgesia					
Yes					
No					
Augmentation of labour					
Yes					
No					
Postpartum haemorrhage (>1000 cc blood loss)					
Yes					
No					
Episiotomy					
Yes					
No					
Third or fourth degree perinatal trauma					
Yes					
No					

Neonatal variables (n=)	Perined data source ^ 1 ^	Perined n (%)	Missing N	Hospital records n (%)	Missing n
Gestational age at delivery (days) *(median (IQR))* ^b^					
Sex					
Boy					
Girl					
Inconclusive					
Birth weight (grams) *(mean (SD))*					
Apgar score 5 minute postpartum <7					
Yes					
No					
If pH-value is determined, value *(mean (SD))*					
Consultation by the paediatrician and/or hospitalization of the neonate					
Yes					
No					
Perinatal death					
No					
Antenatal death					
Natal death					
Neonatal death (up to 7 days postpartum)					

^1^
Final choices for the categorization per variable will be made when doing the analysis. An attempt will be made to stay as close as possible to the Perined categories as used in the Perined data.

^2^
As discussed in the methods section Perined variables can be registered by one healthcare profession, but also by more than one. This column will show the data source(s) of the variable.

**Table 2. T2:** Example|Degree of completeness and the agreement between Perined and hospital records/CRFs to be studied.

Variable					
Maternal and birth variables	Degree of completeness Perined (%)	Percent agreement (%)	Kappa (95% CI) or ICC* (95% CI)	PABAK	Cases (n)
Maternal age					
Maternal ethnicity					
Parity					
Responsible profession at start of labour					
Referral of care from midwife-led care to obstetric-led care during labour					
Responsible profession at birth					
Start of labour					
Type of birth					
Epidural/spinal analgesia					
Augmentation of labour					
Postpartum haemorrhage (>1000 cc blood loss)					
Episiotomy					
Third or fourth degree perinatal trauma					

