### Data collection and selection

Perined data and extracted hospital record data for the planned comparison study are selected using a subsample of the IRIS study.
Figure 2 shows the used data sources for this study. For the IRIS study hospital records were selected for in-depth data collection based on certain criteria for the Perined or survey data. If the Perined record suggested a case of perinatal death (between 28 weeks pregnancy and 7 days postpartum), a low Apgar score (<4) at five minutes, a birth weight between percentile 2.3 and 5 and neonatal hospitalization for more than three days, or a birth weight < percentile 2.3, data from hospital records were extracted. Hospital records were also selected based on a longitudinal survey; a subsample of women in the IRIS study (n= 1949) took part in this survey.
^
21
^ The survey data were used to identify cases at risk for a severe adverse perinatal outcome. When mothers indicated in the survey that they had a consultation or referral of care to obstetrician-led care, or that their baby visited a paediatrician or neonatologist, they were included for the in-depth data collection from hospital records if they met certain criteria. Maternal indications to be included in the in-depth data collection included maternal hospitalization during pregnancy and/or postpartum or maternal hospitalization for more than 48 hours after birth without medical intervention or an hospitalization of more than 72 hours related to a caesarean section.
^
25
^ Trained research assistants performed the data extraction. After data extraction from the hospital records, the amount of error in data entry was analysed. Double entry analyses were performed on hospital records of 111 women. The incidence of data entry error was 3.2% overall, 3.7% for maternal data and 2.6% for neonatal data.
^
19
^

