** *Neonatal variables* **					
Gestational age at birth (in days)					
Sex					
Birth weight (in grams)					
Apgar score 5 minutes postpartum <7					
pH-value umbilical cord determined					
If pH-value is determined. value					
Consultation by the paediatrician and/or hospitalization of the neonate					
Perinatal death					
No					
Antenatal death					
Natal death					
Neonatal death (up to 7 days postpartum)					

Records with missing data for some of the variables will be included in the planned study, to assess the degree of completeness of the different variables in Perined.

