### Statistical analyses

The data in the IRIS study are not always coded in the same way as those in Perined. Recoding of the variables will be necessary to make comparisons possible, this will be done in
Rstudio 4.2.1 and
IBM SPSS statistics 28. We will stay as close as possible to the Perined categories. If too much recoding is required to compare the variables, no comparison will be considered. All statistical analyses will be performed in Rstudio 4.2.1. PABAK will be calculated in Rstudio 4.2.1 with the formula 2*((a+d)/(a+b+c+d))-1, based on a 2x2 table.
^
26
^ For ordinal scales, PABAK will be calculated using the
PABAK-OS calculator.
^
27
^

By using descriptive statistics, frequencies and percentages will be presented for all categorical variables. For continuous variables (e.g. birthweight, Apgar score) with a normal distribution, means and standard deviations (SD) will be calculated. Medians and interquartile ranges (IQR) will be reported for continuous variables not normally distributed.

The completeness of the selected variables in Perined will be calculated as the number of patients with information recorded in Perined divided by the total number of patients in the hospital records dataset or CRF based dataset.

The agreement of the categorical variables will be assessed as the percent agreement and Cohen’s Kappa with 95% confidence interval (CI). Cohen’s Kappa is a statistical measure for dichotomous, categorical and nominal variables to examine the proportion of agreement corrected for the proportion of agreement that could be expected by chance.
^
8
^
^,^
^
28
^ The following criteria to assess the strength of agreement will be used: Kappa coefficient ≤ 0 poor, 0.01-0.20 slight, 0.21-0.40 fair, 0.41-0.60 moderate, 0.61-0.8 substantial, 0.81-0.99 almost perfect.
^
29
^
^,^
^
30
^ The advantage of using Kappa as a measure of agreement is the correction for chance. The disadvantage of using Kappa is the extreme sensitivity for unequal distributions. When one of the values is very common and the other very rare, Kappa is drastically lowered, even when the agreement is high, this is defined as the Kappa’s paradox.
^
31
^ Therefore, the ‘Prevalence-Adjusted-Bias-Adjusted-Kappa’ (PABAK) will also be calculated for all categorical variables as this measure can account for unequal distributions of the test variables.
^
26
^ For PABAK, the same strength of agreement criteria as for KAPPA will be used.

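### Four conditional maternal variables have no stated eligible group for agreement, so women who could not have the event may inflate percent agreement and PABAK

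*Protocol article*

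**What the plan says.** The agreement rows are in the protocol article, Methods, 'Data collection and selection', Tables 1 and 2. Four of them describe events that only some mothers can have: "Referral of care from midwife-led care to obstetric-led care during labour", augmentation of labour, episiotomy, and "Third or fourth degree perinatal trauma" (read here as perineal trauma). Table 1 gives each only the levels Yes and No, with no 'not applicable' level, under one block heading that begins "Maternal variables (n". The text above the tables says the authors expect the data to fit the categories shown.

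The same block includes women who cannot have some of these events. "Responsible profession at start of labour" has an obstetric-led level, and "Planned caesarean section" is a level of both start of labour and type of birth.

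One variable is made conditional: Table 2 has a row for whether cord pH was determined and a further row, "If pH-value is determined. value".

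'Statistical analyses' says "The agreement of the categorical variables will be assessed as the percent agreement", together with kappa and, for categorical variables, PABAK. It gives a whole-dataset denominator for completeness and names none for agreement. PABAK is graded on the same bands as kappa: 0.61-0.8 substantial, 0.81-0.99 almost perfect.

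**The concern.** A woman already in obstetric-led care at the start of labour cannot be referred from midwife-led care during it. A woman with a planned caesarean has no labour to augment. Episiotomy and third/fourth degree trauma concern vaginal births. With only Yes and No available, the natural code for these women is 'No' in both sources. Such a pair scores as a correct registration but says nothing about how well Perined records the event when it can happen.

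The study is meant to help researchers choose Perined variables as outcomes. A variable recorded moderately well among eligible women could be labelled 'almost perfect' because many women in the table were never eligible. The ineligible may be numerous: the hospital-record subsample is selected partly on contact with obstetrician-led care and on "an hospitalization of more than 72 hours related to a caesarean section".

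**Working it through.** The documents give no expected agreement, prevalence or ineligible share, so there is no plan figure to reproduce. The formulas are standard or the plan's own; every input share below is an assumption.

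**Formulas.** For a 2x2 table with cells a (Yes/Yes), b, c (discordant) and d (No/No), n = a+b+c+d:
- agreement po = (a+d)/n
- PABAK = 2·po − 1 (the plan's formula)
- kappa = (po − pe)/(1 − pe), with pe the chance agreement from the margins.

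**Direction.** Add ineligible women to d and hold a, b, c fixed. If there is any discordance, po and PABAK rise towards 1. Kappa can be written 2(ad − bc)/[(2a+b+c)d + b(a+b) + c(a+c)]. It also rises with d, but only towards 2a/(2a+b+c).

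**Referral.** Assume half the women are eligible, 70% of these are referred, agreement among them is 85%, and errors are symmetric.
- Eligible only: po = 0.85; pe = 0.70² + 0.30² = 0.58; kappa = 0.27/0.42 = 0.643; PABAK = 0.70.
- All women: po = 0.5×0.85 + 0.5 = 0.925; share of Yes 0.35; pe = 0.35² + 0.65² = 0.545; kappa = 0.38/0.455 = 0.835; PABAK = 0.85.
- With 30% referred instead of 70%, the eligible-only values are the same. Over all women the share of Yes is 0.15, pe = 0.745, kappa = 0.18/0.255 = 0.706, PABAK = 0.85.

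**Episiotomy.** Assume 25% episiotomy and 88% agreement among vaginal births.
- Eligible only: pe = 0.25² + 0.75² = 0.625; kappa = 0.255/0.375 = 0.680; PABAK = 0.76.
- 30% caesarean: po = 0.7×0.88 + 0.3 = 0.916; share of Yes 0.175; pe = 0.711; kappa = 0.709; PABAK = 0.832.
- 40% caesarean: po = 0.928; share of Yes 0.15; pe = 0.745; kappa = 0.718; PABAK = 0.856.

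**A rarer event.** Assume 10% prevalence and 90% agreement among eligible women, with half the set ineligible. Kappa goes from 0.08/0.18 = 0.44 to 0.045/0.095 = 0.47, and PABAK from 0.80 to 0.90.

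**If the added pairs are not all No/No.** Take 80% agreement and 50% prevalence among eligible women (kappa 0.60, PABAK 0.60), with half the set ineligible:

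| Discordance among ineligible | Agreement | Kappa | PABAK |
|---|---|---|---|
| 0% | 90% | 0.73 | 0.80 |
| 10% | 85% | 0.62 | 0.70 |
| 20% | 80% | 0.52 | 0.60 |

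The inflation therefore depends on ineligible women agreeing better than eligible women.

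**The case against.** A reader might infer that the plan computes agreement over all mothers. No sentence says so. The single n heads Table 1, which is descriptive; Table 2 has its own 'Cases (n)' per row; both tables are labelled as examples; and final categorisation is left to the analysis, with the syntax to be published later. Restriction is left open, not ruled out. This stands, and the point is limited to it. But 'Cases (n)' can equally mean the number of non-missing pairs, and no eligibility rule appears anywhere. If ineligible women are instead coded as missing, they lower completeness, whose denominator is the whole reference dataset. The eligible group needs defining on either coding.

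A reader might also extend the point to all labour and birth variables, or to Apgar score and paediatric consultation. That is not supported. Start of labour, type of birth, responsible profession at birth, postpartum haemorrhage and epidural/spinal analgesia can apply to every mother. A stillborn infant's Apgar score need not be coded 'No'.

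The pairs are not automatically No/No. The sources may disagree on who was responsible at the start of labour or on type of birth, and the inflation then shrinks or reverses. This stands too, but it means that errors in another variable enter the referral or episiotomy row, which is a further reason to define eligibility.

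The selection rule does not settle the ineligible share. It can also bring in women referred during labour and unplanned caesareans after labour, who are eligible for some of these events.

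Finally, agreement over all records is a legitimate registry target, since users analyse whole cohorts and a false 'Yes' in an ineligible woman is a real error. Reporting that figure as secondary, with a separate count of such errors, meets this.

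**Conclusion.** The point holds for four variables: referral during labour, augmentation, episiotomy and third/fourth degree trauma. The tables as written give them Yes/No only, in a block containing ineligible women, and state no restriction, while the pH value is made conditional.

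If ineligible women are coded 'No' in both sources, percent agreement and PABAK are inflated. In the referral and episiotomy examples PABAK crosses from 'substantial' to 'almost perfect'. Kappa is affected less: it changes band in the 70% referral example, but not with 30% referred, nor for episiotomy, nor for the rarer event. It would overstate the point to say that all three measures are materially inflated.

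The actual size cannot be derived from the documents. It rests on the ineligible share, the event's frequency and agreement among eligible women, and how far the sources agree on eligibility. No size is offered for augmentation, where only planned caesareans are ineligible and their share is not given.

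**What to change.** For these four variables, compute the main percent agreement, kappa and PABAK among women eligible according to the reference record:
- referral: midwife-led care at start of labour
- augmentation: spontaneous or induced start of labour
- episiotomy and third/fourth degree trauma: vaginal birth, spontaneous or assisted.

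Put the eligible number in 'Cases (n)'. Report the all-records figure as secondary. Count a Perined 'Yes' in a woman ineligible by the reference record separately, as a plausibility error.

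The cost is one filter per variable, using fields already in Tables 1 and 2, plus a smaller n and somewhat wider intervals. As an illustration, suppose all 2884 hospital records contribute and half are eligible (1442). In the referral example, the 95% half-width for percent agreement is 1.96×√(0.85×0.15/1442) = 1.8 percentage points, against 1.96×√(0.925×0.075/2884) = 1.0 over all records.

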** *Neonatal variables* **					
Gestational age at birth (in days)					
Sex					
Birth weight (in grams)					
Apgar score 5 minutes postpartum <7					
pH-value umbilical cord determined					
If pH-value is determined. value					
Consultation by the paediatrician and/or hospitalization of the neonate					
Perinatal death					
No					
Antenatal death					
Natal death					
Neonatal death (up to 7 days postpartum)					

Records with missing data for some of the variables will be included in the planned study, to assess the degree of completeness of the different variables in Perined.

### Statistical analyses

The data in the IRIS study are not always coded in the same way as those in Perined. Recoding of the variables will be necessary to make comparisons possible, this will be done in
Rstudio 4.2.1 and
IBM SPSS statistics 28. We will stay as close as possible to the Perined categories. If too much recoding is required to compare the variables, no comparison will be considered. All statistical analyses will be performed in Rstudio 4.2.1. PABAK will be calculated in Rstudio 4.2.1 with the formula 2*((a+d)/(a+b+c+d))-1, based on a 2x2 table.
^
26
^ For ordinal scales, PABAK will be calculated using the
PABAK-OS calculator.
^
27
^

By using descriptive statistics, frequencies and percentages will be presented for all categorical variables. For continuous variables (e.g. birthweight, Apgar score) with a normal distribution, means and standard deviations (SD) will be calculated. Medians and interquartile ranges (IQR) will be reported for continuous variables not normally distributed.

The completeness of the selected variables in Perined will be calculated as the number of patients with information recorded in Perined divided by the total number of patients in the hospital records dataset or CRF based dataset.

The agreement of the categorical variables will be assessed as the percent agreement and Cohen’s Kappa with 95% confidence interval (CI). Cohen’s Kappa is a statistical measure for dichotomous, categorical and nominal variables to examine the proportion of agreement corrected for the proportion of agreement that could be expected by chance.
^
8
^
^,^
^
28
^ The following criteria to assess the strength of agreement will be used: Kappa coefficient ≤ 0 poor, 0.01-0.20 slight, 0.21-0.40 fair, 0.41-0.60 moderate, 0.61-0.8 substantial, 0.81-0.99 almost perfect.
^
29
^
^,^
^
30
^ The advantage of using Kappa as a measure of agreement is the correction for chance. The disadvantage of using Kappa is the extreme sensitivity for unequal distributions. When one of the values is very common and the other very rare, Kappa is drastically lowered, even when the agreement is high, this is defined as the Kappa’s paradox.
^
31
^ Therefore, the ‘Prevalence-Adjusted-Bias-Adjusted-Kappa’ (PABAK) will also be calculated for all categorical variables as this measure can account for unequal distributions of the test variables.
^
26
^ For PABAK, the same strength of agreement criteria as for KAPPA will be used.

For continuous variables, the agreement between Perined and the extracted hospital record data will be assessed using the percent agreement and intra-class correlation coefficient (ICC) with 95% CI. The ICC is a correlation coefficient which tests whether there is agreement between two continuous variables measuring the same outcomes in two different data sources. The ICC is an appropriate statistical measure of reliability for continuous data.
^
32
^ ICC values range between 0 (no agreement) and 1 (total agreement). The following criteria to assess the level of agreement will be used: < 0.5 poor, 0.5-0.75 moderate, 0.75-0.9 good, > 0.90 excellent.
^
32
^

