## Methods

### Design

This research protocol depicts a data comparison study concerning a subsample of data based on the IRIS study.
^
19
^
^,^
^
21
^ To assess agreement, data from Perined will be compared with data extracted from hospital records from the participating mothers and/or neonates or with demographic baseline data collected via Case Report Forms (CRFs) at enrolment of participating women (around 22 weeks’ gestation) completed by the midwives together with the participants.
^
19
^
^,^
^
21
^ The data extracted from the hospital records and CRF-based demographics of the IRIS study are used as reference standards. In short, the IRIS study was a multi-centre nationwide stepped wedge cluster randomized trial investigating the effectiveness of routine ultrasound screening in the third trimester of pregnancy in reducing severe adverse perinatal outcomes in low risk pregnancies.
^
19
^ Routine third trimester ultrasound screening was compared with standard care. Sixty primary care midwifery practices in the Netherlands and a total of 13,520 women with a low risk singleton pregnancy participated in the IRIS study. The women were enrolled between February 2015 and February 2016. Data of 13,024 (96.3% of 13,520) participating mothers and neonates were linked to Perined data.
^
19
^ Data extracted from the hospital records (n=2884) were collected for neonates at risk for severe adverse perinatal outcomes and for mothers with an at risk neonate and/or with indications of peripartum pathology or hospitalization (see section
*data collection and selection* for more details and variable operationalization).

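### PABAK, a rescaled percent agreement for binary variables, is read on kappa's bands, so its label can contradict kappa for uncommon outcomes, with no rule for which prevails

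*Protocol article*

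**What the plan says.** All points below are in the Protocol article, Statistical analyses, unless stated.

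- Main measures for categorical variables: "The agreement of the categorical variables will be assessed as the percent agreement and Cohen’s Kappa with 95% confidence interval (CI").
- Why PABAK is added: when one value is very common and the other rare, "Kappa is drastically lowered, even when the agreement is high, this is defined as the Kappa’s paradox". PABAK therefore "will also be calculated for all categorical variables as this measure can account for unequal distributions" of the variables.
- How it is computed: "PABAK will be calculated in Rstudio 4.2.1 with the formula 2*((a+d)/(a+b+c+d))-1, based on a 2x2 table". Ordinal scales go to a separate calculator.
- How kappa is labelled: from "Kappa coefficient ≤ 0 poor, 0.01-0.20 slight" up to "0.61-0.8 substantial, 0.81-0.99 almost perfect".
- How PABAK is labelled: "For PABAK, the same strength of agreement criteria as for KAPPA will be used".
- Status of the comparator (Design): "The data extracted from the hospital records and CRF-based demographics of the IRIS study are used as reference standards".

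The Table 2 shell has columns for completeness, percent agreement, kappa or ICC with CI, PABAK and number of cases. The Table 1 shell shows counts and missing values from each source side by side.

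**The concern.** Kappa's verbal bands were chosen for a coefficient that corrects for chance agreement at the observed prevalences. The plan's PABAK drops that correction. For a rare outcome it is dominated by the records in which both sources say no. Its label then says little about whether the cases themselves are recorded.

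The study is meant to help researchers choose Perined variables as outcomes (Conclusion and discussion). Postpartum haemorrhage, third or fourth degree trauma and a low Apgar score are the kind of row where a user needs to know how many cases the registry misses and how many it records wrongly. If such a row carries one label from kappa and the opposite label from PABAK, and the text has already explained a low kappa as a paradox, the reader is led towards the favourable label.

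**Working it through.** **Inputs.** The PABAK formula and the bands are from Statistical analyses. N = 2884 is the hospital-record sample (Design); paired numbers per variable will be smaller where data are missing. The documents give no prevalences, so those below are assumed. The plan states no figure of its own to reproduce here.

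Notation: a = case in both sources; b = case in Perined only; c = case in the reference only; d = case in neither.

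**1. PABAK is percent agreement rescaled.** With po = (a+d)/N, PABAK = 2po − 1. The top band starts at 0.81: 2po − 1 ≥ 0.81 gives po ≥ 0.905.

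**2. Total miss.** If Perined records no case and has no false positives, po = 1 − p, so PABAK = 1 − 2p. Kappa is 0, because observed and expected agreement are equal. PABAK ≥ 0.81 holds for p ≤ 0.095.

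| Assumed prevalence | Cases of 2884, all missed | PABAK | Kappa |
|---|---|---|---|
| 2% | 58 | 0.960 | 0 |
| 5% | 144 | 0.900 | 0 |
| 9.5% | 274 | 0.810 | 0 |
| 10% | 288 | 0.800 (next band down) | 0 |

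With 1% false positives added, PABAK is still 0.940 at 2% and 0.881 at 5%; kappa is −0.013 and −0.016.

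**3. Partial miss.** With half the cases missed and no false positives, po = 1 − p/2, so PABAK stays at or above 0.81 up to p = 0.095/0.5 = 19%. At 2% prevalence (a = 29, c = 29), PABAK is 0.980 and kappa 0.66. Sensitivity is 50% (Wilson 95% CI 37.5% to 62.5%).

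**4. Different errors, same PABAK.** Each table below has 58 disagreements, so PABAK = 1 − 2 × 58/2884 = 0.960 throughout. Kappa = (po − pe)/(1 − pe), with po = 2826/2884 = 0.9799.

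| a, b, c, d | Kappa | Sensitivity a/(a+c) | PPV a/(a+b) |
|---|---|---|---|
| 0, 0, 58, 2826 | 0 | 0% (95% CI 0 to 6.2%) | undefined |
| 29, 29, 29, 2797 | (0.9799 − 0.9606)/0.0394 = 0.49 | 50% | 50% |
| 58, 0, 58, 2768 | (0.9799 − 0.9413)/0.0587 = 0.66 | 50% | 100% |
| 58, 58, 0, 2768 | 0.66 | 100% | 50% |

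Kappa separates the first two rows from the others. Neither coefficient separates the last two, where Perined under-records in one and over-records in the other.

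**The case against.** A reader might infer that the plan would pass off a useless registry variable as almost perfect, or that its planned output cannot show under-recording. The documents do not support either reading.

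- Kappa is kept, with a 95% CI, in the same Table 2 row. In the total-miss case it would fall in the lowest band.
- Table 1 would show 0 cases in Perined beside 58 in the hospital records. For a binary variable with complete data, the two totals and percent agreement even recover the whole 2×2 table. In the second row of the last table, a = (58 + 58 − 58)/2 = 29. Missing values and rounding make this approximate, and the reader has to do it, but the information is largely there.
- Prevalences are unknown, and the sample is enriched for at-risk neonates and for mothers with peripartum problems. Above 9.5% a total miss no longer earns the top label.
- Perinatal death has four categories in the shells, so the 2×2 result applies only if it is dichotomised. A death or a five-minute Apgar score below 4 in Perined itself triggers record extraction (Data collection and selection), so a total miss is not a realistic pattern for those variables.
- The stated aim is completeness and agreement, both tables are marked as examples, and a fuller analysis plan may exist. The absence of sensitivity and PPV is therefore not an error in itself.

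All of this stands, and it limits the point. It does not rescue the shared bands. They are a stated rule, they fail exactly where PABAK is offered as the remedy, and nothing says how to resolve two opposing labels.

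**Conclusion.** The point holds as a labelling fault of moderate weight. For binary variables the PABAK label depends on percent agreement alone: 90.5% suffices for the top band, whatever happens to the cases. The contradiction with kappa is at its widest for outcomes at or below 9.5% prevalence, where complete non-recording gives the top label on one coefficient and the bottom on the other. The thresholds are algebra. Which variables in this sample fall below 9.5% is not stated, and the worked examples assume their prevalences.

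The symmetric coefficients also do not directly report the direction of error, although named reference standards make that possible. No test or decision rule in the plan depends on the PABAK label. The harm is to the wording of the conclusions and to how users read them.

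**What to change.** 1. Delete the sentence that applies kappa's bands to PABAK. Report PABAK, if kept, without a verbal label.
2. For binary variables, and for nominal categories taken one against the rest, add sensitivity, specificity, PPV and NPV of Perined against the reference, or positive and negative specific agreement, with 95% CIs. Base statements about uncommon outcomes on these together with kappa.
3. For variables tied to the Perined selection criteria (perinatal death, Apgar score, low birth weight if dichotomised), report PPV and do not interpret sensitivity, because entry to the sample depended on the Perined value. For Apgar the trigger is below 4 while the tabulated variable is below 7, so even the PPV describes the selected sample.
4. State that the reference is imperfect. Double entry for 111 women found data-entry error of 3.7% for maternal and 2.6% for neonatal data. That exceeds the 2% prevalence assumed above, so it can distort sensitivity and PPV for rare outcomes.

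Cost: a few lines of R and extra columns in Table 2, with no new data. The table becomes larger, and the wording for some uncommon outcomes will be less favourable.

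### For continuous variables the plan reports percent agreement and a banded ICC, but nothing that shows how large record-level differences are

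*Protocol article*

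**What the plan says.** The Statistical analyses section of the protocol article states that agreement on continuous variables "will be assessed using the percent agreement and intra-class correlation coefficient (ICC) with 95% CI". The ICC is then graded on a fixed scale: "< 0.5 poor, 0.5-0.75 moderate, 0.75-0.9 good, > 0.90 excellent". It is introduced as follows: "The ICC is a correlation coefficient which tests whether there is agreement between two continuous variables", and a value of 1 is said to mean complete agreement. The section does not say whether the absolute-agreement or the consistency form is meant, or how percent agreement is counted for a continuous quantity.

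The Table 2 shell has columns for completeness, percent agreement, Kappa or ICC with its interval, PABAK and number of cases. Its continuous rows are maternal age, gestational age in days, birth weight in grams and, where measured, cord pH. No column holds a paired difference.

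The Table 1 shell sets Perined and the reference source side by side. For continuous variables "with a normal distribution, means and standard deviations (SD) will be calculated", with medians and interquartile ranges otherwise.

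The closing discussion says the results should help researchers choose Perined outcome variables, and help Perined and software developers improve data collection and extraction.

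**The concern.** The ICC is a ratio: disagreement between the sources set against the spread between people. It has no units. Where people differ widely, as on birth weight or gestational age, a high ICC can coexist with differences that matter to someone using the variable. Selecting records partly on very low birth weight may widen that spread and raise the ICC further.

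A researcher deciding whether to use Perined birth weight or gestational age needs to know by how many grams or days a record may be off, and in which direction. If the published table gives only a percentage and a graded ICC, a variable can be labelled excellent while that question goes unanswered.

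**Working it through.** The plan states no expected ICC and no SDs, so there is no figure of its own to reproduce. The SDs below are assumptions, shown as ranges: birth weight 500-700 g, gestational age 10-18 days, pH 0.08-0.10.

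**Sporadic differences.** If a share f of records differs by +d or -d at random, ICC = SD² / (SD² + f·d²/2).

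- Birth weight, f = 10%, d = 500 g, so f·d²/2 = 12,500. SD 500: 250,000/262,500 = 0.952. SD 600: 360,000/372,500 = 0.966. SD 700: 490,000/502,500 = 0.975.
- Gestational age, f = 20%, d = 7 days, so f·d²/2 = 4.9. SD 10: 100/104.9 = 0.953. SD 14: 196/200.9 = 0.976. SD 18: 324/328.9 = 0.985.

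**Uniform shift s, absolute-agreement form.** ICC = SD² / (SD² + s²/2).

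- s = 200 g, s²/2 = 20,000: 250,000/270,000 = 0.926; 360,000/380,000 = 0.947; 490,000/510,000 = 0.961.
- s = 500 g, s²/2 = 125,000: 0.667, 0.742 and 0.797, so not excellent.
- s = 7 days, s²/2 = 24.5: 0.803, 0.889 and 0.930, so excellent only at the widest SD.

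Simulating 2,884 pairs (100 replicates) gave the same values to within 0.001. That number is the article's count: "Data extracted from the hospital records (n=2884) were collected for neonates at risk" and for certain mothers, so the number of pairs for a given variable may be smaller.

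**How much the top band tolerates.** Setting the ICC to 0.90 gives f = 2·SD²/(9·d²). For 500 g differences this is 22% of records at SD 500 and 44% at SD 700. For 7-day differences it is 45% at SD 10 and 89% at SD 14; at SD 18 the formula exceeds 1, so every record could be wrong by 7 days. In terms of limits, an ICC of 0.90 with no bias and equal variances gives 95% limits of ±1.96·√0.2·SD = ±0.877·SD. That is ±438 to 614 g, ±8.8 to 15.8 days, or ±0.07 to 0.09 pH units.

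**What the other planned outputs would show.**

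- Percent agreement, if counted as exact match, would be about 90% in the birth-weight example and 80% in the gestational-age example. That gives the frequency of differences, not their size. On the same reading, harmless rounding of every weight from 1 g to 10 g gives about 10% agreement with an ICC of 1.000.
- Table 1 would show a uniform shift. Offsetting errors leave the mean unchanged and barely move the SD: in the 10% example the Perined SD is √(SD² + 25,000), that is 500 to 524, 600 to 620, or 700 to 718 g. Gestational age is shown there as a median, which symmetric errors do not move.

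**What a difference summary would show.**

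- Birth-weight example: the SD of the differences is √(0.10 × 500²) = 158 g, giving limits of ±310 g. With 5% of records wrong in each direction, the 2.5th and 97.5th percentiles are -500 and +500 g. With 2,884 pairs the 95% CI of the mean difference would be about ±1.96 × 158/√2,884 = ±5.8 g.
- Gestational-age example: the SD is √(0.20 × 49) = 3.13 days, giving limits of ±6.1 days and percentiles of -7 and +7 days.

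**The case against.** The ICC is not the sole yardstick. The abstract names percent agreement as the reliability measure and adds the ICC to it, and Table 2 gives percent agreement its own column. A reader would see 80% or 90% beside the high ICC and know that something differs. This stands: the frequency of differences is not hidden. Their size is.

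Table 1 puts means or medians from both sources side by side, so a large constant shift would be seen, with its direction. This also stands, at group level. Table 1 cannot show offsetting differences and gives no interval for the paired difference.

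A reader might infer that percent agreement means exact match, so that harmless rounding would look like failure. The article does not say so; it leaves the term undefined for continuous data. A reader might also infer that the ICC ignores any constant shift. That is true only of the consistency form. The article's language of agreement, with 1 as complete agreement, points rather to the absolute-agreement form, under which a 500 g shift would not be graded excellent. Both details may sit in a fuller plan, and their absence from an article is not itself a fault.

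Finally, the examples depend on assumed SDs. That is so, but the sporadic-difference results and the 200 g shift stay above 0.90 across the whole assumed range.

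**Conclusion.** The point holds in a limited form. The article fixes the measures, the grading bands and the result columns for continuous variables, and none of them shows the size or spread of record-level differences. Under the assumed SDs, the top band is reached with 500 g differences in 10% of weights, 7-day differences in 20% of gestational ages, or a uniform 200 g shift under absolute agreement. These figures assume that differences are unrelated to the true value and, for the sporadic cases, equally likely in either direction.

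The documents do not support the stronger reading that the plan would miss systematic error altogether, or that the ICC band overrides percent agreement. Nor do they show that the ICC is the wrong statistic; making it secondary would be a preference. What is missing is a summary in grams, days, years and pH units beside it, which the study's stated use of guiding the choice of variables needs.

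**What to change.** Add to Table 2, for each continuous variable:

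1. The mean paired difference, Perined minus reference, with 95% CI.
2. The Bland-Altman 95% limits of agreement or, if most differences are zero, the 2.5th and 97.5th percentiles of the differences.
3. Percent agreement, both exact and within a tolerance fixed before the sources are compared, at the coarser recording precision of the two.

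The third item also covers a gap in the second: the percentiles will both be zero if fewer than 2.5% of records differ in each direction.

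State that the ICC is the absolute-agreement form. Keep its bands, but do not call a variable excellent without the difference summary beside it. Describe the results as differences from the reference rather than as Perined errors, because the reference has its own: "The incidence of data entry error was 3.2% overall, 3.7% for maternal data and 2.6% for neonatal data".

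The cost is a few lines of code, a few extra columns and agreeing the tolerances in advance. No new data are needed.
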